# A manual-based vocational rehabilitation program for patients with an acquired brain injury: study protocol of a pragmatic randomized controlled trial (RCT)

**DOI:** 10.1186/s13063-017-2115-0

**Published:** 2017-08-10

**Keywords:** Traumatic brain injury, Vocational rehabilitation, Caregiver intervention, Return to work, Randomized controlled trials, Study protocol

## Abstract

**Background:**

An acquired brain injury (ABI) is a complex injury often followed by a broad range of cognitive, physical, emotional, and behavioral disabilities. Because of these disabilities, vocational rehabilitation (VR) is a challenging task, however, of great importance, since approximately 75% of the patients with ABI are of working age. Thus, standardized clinically effective and cost-effective methodologies regarding VR for patients with ABI are highly needed. Therefore, the aim of this study is to evaluate the effect of an individually targeted manual-based VR for patient with ABI compared to conventional VR (usual care).

**Methods:**

This study is an interventional, two-arm, six-month follow-up, cluster randomized controlled trial involving four municipalities in the Zealand Region and the Capital Region of Denmark. A total of 84 patients with ABI evenly distributed across four municipalities will be included in the study. The patients will randomly be allocated in a 1:1 ratio to the VR intervention provided by a specialized Brain Injury Centre or the conventional VR provided by the municipalities (usual care). The six- to nine-month intervention will consist of individual and group therapies as well as a work placement program including supported employment. Furthermore, the intervention will include a family intervention program followed up by support to one individual family caregiver. The primary outcomes are increased work or study rate at six-month follow-up. Moreover, a budget impact analysis and possibly a cost-utility analysis of the intervention will be performed.

**Discussion:**

This study consists of a comprehensive multidiciplinary VR intervention involving several parties such as the municipalities, a specialized rehabilitation team, and patients’ own family caregivers. If this intervention is proven successful when compared to the conventional VR, it will provide evidence for a manual-based individualized holistic approach in returning to work after an ABI. Furthermore, the study will contribute with novel knowledge regarding feasibility and clinical effectiveness of the VR intervention relevant to clinicians, researchers, and policymakers.

**Trial registration:**

ClinicalTrials.gov, NCT03086031. Registered on 21 March 2017.

**Electronic supplementary material:**

The online version of this article (doi:10.1186/s13063-017-2115-0) contains supplementary material, which is available to authorized users.

## Background

An acquired brain injury (ABI) is a complex injury often followed by a broad range of cognitive, physical, emotional, and behavioral disabilities [1, 2]. Because of these disabilities, most patients with ABI find it challenging to remain in or return to work post injury [3–5], even though approximately 75% of these patients are of working age [6].

Vocational rehabilitation (VR) is often a prolonged process, leading to high cost to the healthcare system and society [7]. Barriers to VR success include the severity of the ABI, age at injury, income, and education pre injury, but also challenges directly related to the workplace [1, 8, 9]. Often, the employer has little or no knowledge about the consequences of an ABI and there is no direct communication between the brain injury specialist, the employer, and the employees regarding the challenges and needs in relation to work-related tasks.

Even though returning to work has proven important for long-term ABI survival and increased levels of quality of life [10], standardized evidence-based VR programs targeting patents with ABI have been lacking [11–13]. One very interesting feasibility randomized controlled trial (RCT) protocol has been published regarding brain injury and return to work; however, this protocol involved patients with a traumatic brain injury exclusively [14]. It has previously been shown that support from specialized VR teams help patients with ABI returning to work post injury [1, 2]. However, only few studies have examined the long-term effect of different types of VR interventions [5, 13, 15–20]. Such studies have mainly focused on VR programs where multiple unstandardized components interact in time, which challenge the reproducibility and knowledge of the active modules involved. Moreover, the previous VR interventions have been performed similarly to all patients even though ABI is a broad diagnostic category with various degrees and characteristics. Thus, VR interventions that are tailored and adjusted to each patient might be proven more efficient and effective in enhancing returning to work.

The bidirectional relationship between the wellbeing of the patient and the family is well documented [21–29]; consequently, active participation from family caregivers is likely to show a positive effect on the reintegration of the patient in a work setting. Thus, family caregivers could be a valuable resource both in parallel to the professional support and to ensure future consolidation and anchoring of the VR.

In this study, we hypothesize that patients with ABI need a coordinated effort across multiple disciplines and sectors with specialized knowledge (such as municipalities, family caregivers, and rehabilitation teams) in order to get a coherent VR program. Therefore, the aim of this study is to develop an individually targeted manual-based VR program based on thoroughly described modules that inform clinicians, researchers, and policymakers about effectiveness and costs of the VR intervention.

## Methods/Design

### Trial design and hypotheses

An interventional, two-arm, six-month follow-up, cluster RCT (Fig. 1) including 84 participants with an ABI allocated randomly (allocation ratio 1:1) to the VR intervention and control group that consists of a conventional VR program (usual care).

**Fig. 1 Fig1:**
[figure not shown]
A *flow chart* of the study

The main objective of the study is to develop an individually targeted manual-based VR program and determine its efficacy for patients with ABI. The first hypothesis of the study is that more participants allocated to the VR intervention group will have a significant higher employment or study rate (measured in hours) at six-month follow-up when compared to participants receiving the conventional VR program provided by the municipalities (control group). The second hypothesis is that health-related quality of life (HRQoL) and disability among the participants and HRQoL and the caregiver burden among the caregivers are significantly improved at the end of the VR intervention and at six-month follow-up when compared to the conventional VR program. Finally, a budget impact and possibly a cost-utility analysis will be performed since we hypothesize that it will be an economically sound decision for the municipalities to invest in a specialized VR when compared to the conventional VR program provided by the municipalities. Such an analysis is based on an overall assessment of the health gain, both in terms of clinical effects and participant perceived utilities, and the related expenditures and costs.

The duration of the study is three years and the assessments will take place at baseline and at the end of the intervention (approximately after 6–9 months). In order to determine any long-term effect of the intervention, follow-up assessment is planned after six months.

The trial is designed and reported according to the SPIRIT (Standard Protocol Items: Recommendations for Interventional Trials) Statement [30] (see Additional files 1 and 2 and Fig. 2).

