### A description of the manual-based VR interventions

This manual-based VR study comprises the following three phases:Initial assessment: Within two weeks after the referral to the study, each patient will meet with the case manager in the municipality (brain injury coordinator). Here, a more thorough interview will ensure that the inclusion criteria are met and, in addition, asses the patient’s readiness for VR. Moreover, the participant will be fully informed about the content of the study, how participation is voluntary, and how they are free to withdraw at any time during the study. If written informed consent is obtained, each patient is assigned a unique trial ID number and baseline questionnaires will be filled out together with the following socio-demographic, employment, and clinical data: gender; date of birth; residence; civil status; nationality; income; pre-injury employment and education status; pre-injury occupation status; length of education; time since the brain injury; type and location of the brain injury; number of days hospitalized; the date of discharge; clinical diagnoses or any relevant medical events; and alcohol consumption or abuse. Participants will then be randomly assigned to either the VR intervention or the conventional VR. At last, each patient included in the VR intervention group will be asked to choose at least two family members to participate in the family intervention and one family caregiver which will participate actively in the individual sessions and serve as future support and resource facilitator to assist them in returning to work. This initial assessment will take approximately 50 min and the patient will have the opportunity to ask questions throughout the entire assessment. To exclude recruitment bias, patients that meet the eligibility criteria but refuse to participate in the study will be asked a few questions about their refusal. Hereafter, the patient will be contacted by external testers and baseline testing will be completed.The VR intervention program: The VR intervention lasts for a total of 6–9 months and consists of, first, six different modules (approximately three months) that are individually planned based on the patient needs and goals and, second, a work placement program (approximately 3–6 months). To ensure a uniform procedure of each of the different modules, comprehensive “standard operating procedures” (SOPs) will be developed by the rehabilitation team at the Brain Injury Centre before the beginning of the VR intervention. All members of the rehabilitation team (which includes six neuropsychologists, eight occupational therapists, and four physiotherapists) are already experienced in the VR intervention program and exceedingly specialized in ABI rehabilitation. They will go through a one-day workshop to be thoroughly introduced to the specific study protocol and the SOPs as recommended by Holmes et al. [31]. The six modules will be grouped into: (1) individual therapies, which includes neuropsychological sessions (10 h), balance between work and everyday life (20 h), and job matching (10 h); (2) grouped-based therapies, which includes psycho education (18 h), mindfulness (15 h), and physiotherapy training (15 h); (c) a manualized family intervention program (eight sessions of 90 min) [32] and an individual caregiver coaching, supporting the caregiver in assisting the patient using the different strategies and tools learned in the intervention in everyday life and at the workplace (12 h); (4) an individual work placement program including work practice (3–6 months), supported employment where the rehabilitation team is at the work place (30 h), and the development of a post-rehabilitation plan (4 h). The modules are planned based on the participant’s needs and goals thus, the length, duration, structure, and composition of the program will vary from patient to patient. The individual sessions and group sessions are delivered either in parallel or in serial depending on the patient.Group sessions will take place at the Brain Injury Centre BOMI and the individual sessions will most often take place in the patient’s home. The individual work placement intervention will take place at relevant workplaces, the patient’s current workplace, or at a new workplace found by the municipality or the Brain Injury Centre BOMI, depending on the individual case.Post-trial evaluation: An evaluation of the VR intervention will be performed by a self-developed semi-structured interview of each patient. Here, questions related to the recruitment procedure, the modules of the study, the timing of modules, and the coaching by the rehabilitation team will be collected. Furthermore, all case managers at the municipalities that referred participants to the study will be asked about their experiences and level of satisfaction.

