
### The conventional VR provided by the municipalities (usual care)

Individuals allocated to the control group will receive the conventional VR program provided by the municipalities over the same period of time. Thus, the participants in the control group will receive VR support by the local municipal authority that may vary in content and intensity. As for the intervention group, each individual in the control group will select a family caregiver that will go through the same questionnaires as the caregivers in the VR intervention group regarding HRQoL and functional level.

Furthermore, the case manager at the municipalities is obliged to: (1) refer patients to the study; (2) hand out the baseline questionnaires to the participants and their family caregivers; and (3) complete a questionnaire about each participant at the beginning and end of the study, and again at the six-month follow-up.

An evaluation of the conventional VR provided by the municipalities will be performed by the rehabilitation team using a self-developed semi-structured interview of each patient.

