### Outcome measures

Primary and secondary outcomes are outlined in Table 1 and are measured at baseline, after the end of the intervention, and at the six-month follow-up. In addition, the family caregivers will be evaluated (Table 1).

**Table 1 Tab1:** Primary and secondary outcomes and outcomes related to family caregivers

Outcome	Assessment	Test tool	Assessment time:		
			Baseline	End	6-month FU
Primary outcome	Hours at work/study per week	Register-based or by interviews	**X**	**X**	**X**
Secondary outcomes	Proficiency on functional task	The Mayo-Portland Adaptability Inventory (MPAI-4) (participation index – rating will be done separately by the patient, relatives, and staff)	**X**	**X**	**X**
	Functional status	Glasgow Outcome Scale Extended (GOSE)	**X**	**X**	**X**
	Health-related quality of life	EuroQol Five Dimensions Questionnaire EQ-5D-3 L	**X**	**X**	**X**
	Anxiety and depression	Hospital Anxiety and Depression Scale (HADS)	**X**	**X**	**X**
	Fatigue	Dutch Multifactor Fatigue Scale (DMFS)	**X**	**X**	**X**
	Physical functioning	Timed Up and Go (dual task) (TUG)	**X**	**X**	**X**
	Self-perceived burden to others	Self-Perceived Burden Scale (SPB)	**X**	**X**	**X**
	Socio-demographic, employment, and clinical data	Structured interviews	**X**	**X**	**X**
	Working ability	Work Ability Index™ (version 2007)	**X**	**X**	**X**
	Assessment of intelligence	Wechsler Adult Intelligence Scale (subtest)	**X**	**X**	**X**
	Executive functioning	TRAIL Making Test A and B	**X**		
	Cognitive functioning	Paced Auditory Serial Addition Task (PASAT)	**X**	**X**	**X**
	Working memory	Connors Continuous Performance Test	**X**	**X**	**X**
Outcome family caregivers	Quality of life	EuroQol Five Dimensions Questionnaire EQ-5D-3L, SF-12	**X**	**X**	**X**
	The adaptability and cohesion dimensions in family interactions	Family Adaptability and Cohesion Scale (FACES-IV)	**X**	**X**	**X**
	Problem-solving ability	Problem Solving Inventory (PSI)	**X**	**X**	**X**
	Assess perceived burden among caregivers	Caregiver Burden Scale (CBS)	**X**	**X**	**X**
		Hospital Anxiety and Depression Scale	**X**	**X**	**X**

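### The primary visit hangs on an end of intervention that varies over 6–9 months, and the text fixes no matching date for control patients

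*Protocol article*

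**What the plan says.** Trial design and hypotheses sets the first hypothesis as a "significant higher employment or study rate (measured in hours) at six-month follow-up". The same section states that "the assessments will take place at baseline and at the end of the intervention", gives that end as approximately 6–9 months, and adds that "follow-up assessment is planned after six months". Outcome measures says that primary and secondary outcomes "are measured at baseline, after the end of the intervention, and at the six-month follow-up". Table 1 uses the same three columns (baseline, End, six-month follow-up) without separating the arms.

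For the intervention arm, the description of the VR interventions gives a total length of 6–9 months: about three months of modules, then a work placement of about 3–6 months. Content follows each patient's needs and goals, so that "the length, duration, structure, and composition of the program will vary from patient to patient".

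For the control arm, the section on usual care says that patients receive the "conventional VR program provided by the municipalities over the same period of time". It also has case managers complete a questionnaire on each participant at the beginning and end of the study and again at the six-month follow-up. The text shown gives no time from allocation for any post-baseline visit.

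**The concern.** An intervention patient's End visit has a natural date, the day the programme finishes. The length of the placement largely sets that date, and it is decided after allocation by an unblinded team. A control patient has only a period that is itself a three-month range. Whoever books the control visits must choose a point in it, and the text gives no default month, no pairing with a treated patient and no window.

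Patients enter 3–24 months after injury, working or studying at most 15 h/week or not at all, so hours may well change with elapsed time. If the arms differ in mean time from allocation to the primary visit, part of the observed difference in hours reflects time rather than treatment. The economic evaluation is exposed as well: costs are collected to the end of follow-up, and long-term employment is forecast from the effects observed during it.

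**Working it through.** **Timing.** Inputs: End at 6–9 months and follow-up six months later (Trial design and hypotheses), with the order of visits from Outcome measures. If the six months run from End and the programme starts promptly after allocation:

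- earliest primary visit: 6 + 6 = 12 months after allocation
- latest primary visit: 9 + 6 = 15 months
- largest possible difference between two patients: 15 − 12 = 3 months

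**A plausible gap between arm means (assumption).** If intervention lengths spread evenly over 6–9 months, their mean is (6 + 9)/2 = 7.5 months. If all controls were booked at one limit, the gap would be 7.5 − 6 = 9 − 7.5 = 1.5 months. A 3-month gap in means would need every intervention patient at one limit and every control at the other.

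**The plan's own yardstick.** Sample size and power uses 10 versus 14 h/week, overdispersion 4, 42 patients per arm and alpha 0.05, with a stated power of 0.8. With variance = 4 × mean, the standard error is √(4 × (10 + 14)/42) = 1.512 and z = 4/1.512 = 2.646. Two-sided power is Φ(2.646 − 1.960) = 0.754. This does not reproduce 0.8, but that is a separate matter; only the 4 h difference and the variance model are needed here.

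**Illustrative bias.** Bias = drift × gap. The drift is assumed and appears nowhere in the documents.

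| Assumed drift (h/week per month) | Bias at 1.5-month gap | Share of 4 h |
|---|---|---|
| 0.25 | 0.375 h | 9% |
| 0.5 | 0.75 h | 19% |
| 1.0 | 1.5 h | 38% |

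**Effect on error rates, same assumptions.** With no treatment effect and bias b, the standard error is √(4 × (20 + b)/42).

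- b = 0.375: 0.375/1.393 = 0.269, two-sided type I error Φ(0.269 − 1.96) + Φ(−0.269 − 1.96) = 0.058.
- b = 1.5: 1.5/1.431 = 1.048, type I error 0.18.

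If the gap works against the intervention, the apparent difference is 4 − b.

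- 3.625 h: 3.625/1.5 = 2.417, power Φ(2.417 − 1.96) = 0.68.
- 2.5 h: 2.5/1.464 = 1.708, power Φ(1.708 − 1.96) = 0.40.

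Both compare with 0.75 when there is no gap.

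**The case against.** The strongest reply is that this is a journal article condensing a longer protocol. The assessment schedule (Fig. 2), the flow chart and the additional files are not shown, and visit windows are commonly left to such material. That would answer a complaint about a missing window. It does not answer this point, because the article itself states the anchor, gives it as a range and says that length varies by patient. An unseen schedule may still resolve it.

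Three stronger readings are tempting, and the documents do not support them.

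- A reader might infer that usual care has no counterpart to the end of the intervention. It has a nominal one: the same period of time, the same columns in Table 1, and case-manager questionnaires at matching points. What is missing is a rule giving an individual control a date.
- A reader might infer that slow progress lengthens the programme, so that slower intervention patients are given more time. The text ties length to needs and goals and says nothing about extension for slow progress.
- A reader might treat the start of the six-month clock at programme end as stated. It is the natural reading of the visit order, but the text gives no origin.

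Two partial safeguards deserve credit. Hours may be taken from registers, which could allow reading them at a common date. The analysis uses repeated-measures and multilevel methods, which could take account of actual time. The article commits to neither use.

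**Conclusion.** The point holds in a limited form. As written, the plan lets the two arms be assessed at different times since allocation, anywhere from about 12 to 15 months, because the intervention arm's anchor varies by patient and the control arm's is not fixed within the range. The article does not show that the timing will differ, or which arm a difference would favour.

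The figure of 0.4–1.5 h (9–38% of 4 h) rests entirely on an assumed drift of 0.25–1.0 h/week per month and an assumed 1.5-month gap in means. It shows that the matter could be material, not that the result is biased by that amount. The 12–15 month range also assumes that the six months start at the end of the intervention and that the programme starts promptly after allocation. The sponsor should settle the timing, since a common clock removes the ambiguity at little cost.

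**What to change.** Measure the primary outcome at one stated time from allocation in both arms, whenever the programme ended. Fifteen months with a narrow window would do, or an earlier common month. Take hours from registers at that date where available. Set the control End assessment by the same clock from allocation, and preferably use a common End time for the comparison in both arms. An assessment at actual programme end can be kept for intervention patients as descriptive data. This concerns visit dates only; it changes neither treatment length, nor the 84 patients, nor any input to the power calculation.

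The costs are these:

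- Patients who finish early are seen more than six months after programme end. With a 15-month visit and a six-month programme, that is 15 − 6 = 9 months.
- A common End visit no longer coincides with each intervention patient's programme end, so the second hypothesis, which names that time point, needs rewording.
- For patients recruited in August 2018, 15 months falls in November 2019. The present plan already reaches that date for a nine-month programme, but the change would put every late recruit there. Trial status expects follow-up including data analysis to finish by December 2019, so little time is left. A narrow window or an earlier common month would ease this.
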